#### 2.1.1. Recruitment and Eligibility Criteria

Participants are recruited during medical visits in the Allergology, Digestive, Internal Medicine, or Dermatology units of Hospital Clínic of Barcelona, based on the following eligibility criteria: age over 18 years, symptoms associated with histamine intolerance in two or more organs or systems, reduced serum DAO activity and/or any of the DAO-encoding gene variants (rs10156191, rs1049742, rs1049793, and s2052129), not having started a low-histamine diet, and not having taken DAO supplementation. The exclusion criteria are diagnosis of food or environmental allergies, pregnancy, and prescription of antibiotics and/or probiotics within the month prior to recruitment. To assess eligibility, potential participants undergo a questionnaire about histamine intolerance symptoms (Supplementary Figure S1) and an analysis of serum DAO activity and DAO-encoding gene variants, prior to signing an informed consent form (Figure 2). Serum DAO activity is analyzed using a radioimmunoassay technique, with a cut-off value of r < 12.54 U/mL indicating DAO deficiency. Genotyping of the DAO-encoding gene variants is performed by multiplex polymerase chain reaction (PCR) on the buffy coat fraction of blood samples, obtained after the centrifugation of blood collected in an EDTA vacutainer. Both analyses are conducted at the Echevarne Laboratory (Barcelona, Spain).

Eligible participants attend a pre-intervention visit, where the study objectives and procedures are explained in detail, and informed consent for the entire study is signed. Participants also receive a biological sample collection kit (for feces and urine) and instructions for proper collection procedures.

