Therefore, the main objective of this clinical study is to evaluate the efficacy of a low-histamine diet and/or DAO supplementation over a three-month period in improving symptoms of histamine intolerance caused by DAO deficiency. Additionally, the impacts of these dietary strategies on the composition of intestinal microbiota, urinary profile of histamine metabolites, serum DAO activity, and plasma histamine levels will be assessed throughout the intervention.

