#### 2.1.2. Baseline Visit and Randomization of Participants

During the baseline visit, a trained nurse administers a questionnaire to record demographic data and a complete medical history, including alcohol consumption and smoking habits (Supplementary Figure S1). Additionally, participants complete various validated questionnaires specific to each symptom of histamine intolerance (described below). Comprehensive information on dietary habits is collected through a validated 151-item semi-quantitative food frequency questionnaire (FFQ), a seven-day dietary recall (for the seven days prior to the visit), and either a 14-item Mediterranean diet adherence screener (for control diet) or a low-histamine diet screener, administered by trained dieticians in face-to-face interviews [32].

The same trained personnel then collect anthropometric measurements, determine blood pressure (BP), and extract a blood sample to analyze biochemical parameters. Height is measured to the nearest 0.1 cm using a wall-mounted stadiometer, with subjects standing, wearing socks, and maintaining their heads in the horizontal plane. Body weight is recorded to the nearest 0.1 kg, with participants in light clothing, without shoes or accessories, and using a high-quality calibrated scale. Body mass index is calculated by dividing weight (kg) by the square of height (m^2^). Waist circumference is measured midway between the lowest rib and the iliac crest using an anthropometric tape, and hip circumference is measured at the maximum point below the waist, without compressing the skin [33]. BP is taken in triplicate after at least five minutes of rest using a validated semiautomatic oscillometer (Omron HEM-705CP, Hoofddorp, The Netherlands). The clinical analyses include a basic biochemical profile (i.e., glycemia, lipid profile, creatinine, urea, hepatic function parameters, and total proteins and albumin) and serum histamine and tryptase levels. All these analyses are performed in the CORE laboratory of Hospital Clinic following in-house routine procedures and meet all required quality criteria, receiving ISO 9001:2015 certification [34] and ISO 15189:2022 accreditation [35] for some tests.

At this point, participants provide urine and stool baseline samples for the study of metabolomic biomarkers of histamine and intestinal microbiota, respectively (described below). Samples are processed after collection and stored in −80 °C freezers.

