#### 2.1.4. Follow-Up and Final Visits

The evolution of symptoms, urinary profile of histamine metabolites, and intestinal microbiota composition, as well as anthropometric measurements and blood biochemical parameters, including the basic biochemical profile and histamine and tryptase, are assessed after the first and second month (follow-up visits) and the third month (final visit) of the dietary intervention (Figure 2). Serum DAO activity will also be measured during the final visit.

Dietary compliance is assessed using seven-day food records and adherence tests for the low-histamine diet or Mediterranean diet [32]. Unlike the validated Mediterranean diet adherence screener, there is no standard test for assessing compliance with a low-histamine diet. The present research will validate the low-histamine diet adherence test prepared *ad hoc* for this study.

Throughout the intervention period, participants receive a phone call every two weeks to assess correct adherence to the study protocol and to monitor for any unexpected secondary effects.

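### The antibiotic/probiotic exclusion counts only prescriptions and ends at recruitment, so it does not fully protect the later baseline stool sample

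*Protocol article*

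**What the plan says.** Section 2.1.1 lists among the exclusion criteria "prescription of antibiotics and/or probiotics within the month prior to recruitment". The same section places recruitment in the clinic: "Participants are recruited during medical visits in the Allergology, Digestive, Internal Medicine, or Dermatology units". Eligibility is then assessed by a symptom questionnaire, a serum DAO assay and genotyping, both assays being run at an outside laboratory. After that, "Eligible participants attend a pre-intervention visit", and there "Participants also receive a biological sample collection kit (for feces and urine) and instructions for proper collection procedures".

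The baseline visit has its own section (2.1.2). After questionnaires, measurements and blood sampling, "participants provide urine and stool baseline samples for the study of metabolomic biomarkers of histamine and intestinal microbiota". Randomisation by envelope is described next. The article does not state the interval from recruitment to baseline. It describes no repeat of the antibiotic/probiotic check at the baseline visit.

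Microbiota is an additional objective (Introduction: "Additionally, the impacts of these dietary strategies on the composition of intestinal microbiota"). Group differences are to be tested by Kruskal–Wallis (Section 2.2.3), and symptom data are to be correlated with microbiota composition (Section 2.2.1).

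**The concern.** The article does not say why the exclusion exists. The likely reason is to keep recent antibiotic or probiotic use out of the stool profile. For that purpose the wording falls short in two ways.

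- **Anchor.** The protected month ends at recruitment, and the sample comes at least one visit later. Someone who takes antibiotics in the week before the baseline stool can meet every criterion as written.
- **Exposure.** The rule turns on a prescription, so self-taken probiotics do not count. For DAO supplements, the same section asks whether the patient has taken them, not whether they were prescribed.

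At stake are the precision of the microbiota comparison and the meaning of three quantities that use the baseline sample: the baseline profile, change from baseline within a person, and the correlation of symptoms with microbiota.

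**Working it through.** The plan has no figure of its own to reproduce here. The check has two parts.

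**1. Order of events in the text**

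| Step | Section | Covered by the one-month window? |
|---|---|---|
| Month before recruitment | 2.1.1 | Yes, prescriptions only |
| Questionnaire, DAO assay, genotyping | 2.1.1 | Depends on when recruitment counts as complete |
| Pre-intervention visit, stool kit handed out | 2.1.1 | No |
| Baseline visit, stool provided | 2.1.2 | No |
| Randomisation | 2.1.2 | No |

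If recruitment is complete only once the DAO and genotype results are known, the gap shortens. The time from the pre-intervention visit to the baseline stool still lies outside the window.

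**2. Size, on assumed inputs**

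The documents give neither the gap nor the exposure rates. Assume a 6-week gap and 0.2 to 0.5 antibiotic courses per person-year.

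Share exposed in the gap: p = 1 − exp(−rate × time), with time = 6/52 = 0.115 years.

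- Rate 0.2: p = 1 − exp(−0.023) = 2.3%, or 0.023 × 400 ≈ 9 patients, about 1 per group of 50.
- Rate 0.5: p = 1 − exp(−0.058) = 5.6%, or 0.056 × 400 ≈ 22 patients, about 3 per group of 50.

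If exposure is equally common in all groups and shifts a microbiota measure by k SD, variance is multiplied by V = 1 + p(1 − p)k², and the effective group size is 50/V. With k = 1:

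- p = 2.3%: V = 1 + 0.023 × 0.977 = 1.022; 50/1.022 ≈ 49.
- p = 5.6%: V = 1 + 0.056 × 0.944 = 1.053; 50/1.053 ≈ 47.

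A longer gap, or non-prescribed probiotic use, would raise p. A wider range, showing V and effective n of 50:

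| p | k = 0.5 | k = 1 | k = 2 |
|---|---|---|---|
| 2% | 1.005; 49.8 | 1.02; 49.0 | 1.078; 46.4 |
| 5% | 1.012; 49.4 | 1.048; 47.7 | 1.19; 42.0 |
| 10% | 1.022; 48.9 | 1.09; 45.9 | 1.36; 36.8 |
| 20% | 1.04; 48.1 | 1.16; 43.1 | 1.64; 30.5 |

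The formula concerns means. For a rank test such as Kruskal–Wallis it is only a guide.

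For within-person change, suppose every exposed patient is shifted by k SD at baseline and recovers fully. The average change then contains p × k SD that owes nothing to treatment. With k = 1 that is 0.023 to 0.056 SD, the same in expectation in every group.

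**The case against.** The case for leaving the criterion alone has real weight.

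- **The meaning of recruitment is open.** Patients are recruited on criteria that include laboratory results, and the sample-size paragraph (Section 2.1) uses the word loosely for enrolment. This shortens the gap. It does not close it, because Section 2.1.1 ties recruitment to clinic visits, while the baseline visit and randomisation follow under a separate heading.
- **Randomisation protects the group comparison.** A reader might infer that recovery from a disturbed baseline would pass for a diet or supplement effect. The documents do not support that. The baseline stool is described before randomisation, exposure before that point is balanced in expectation, and recovery would occur in the placebo and control-diet groups too. The stated test compares groups; it is not an uncontrolled before-after contrast.
- **Follow-up samples.** A reader might also infer that month 1, 2 and 3 samples taken soon after antibiotic or probiotic use all enter the analysis, with bias if self-use differs between diet groups. Section 2.2.3 does not say which samples or time points are analysed. Rules on concomitant use and on exposed samples may stand in the full protocol or SAP, which are not shown. Differential use between diet groups is conjecture.
- **The outcome is additional.** Nothing here affects the main objective, which is symptoms.

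These arguments limit the point to the baseline sample and to a small effect. They do not answer the wording: the article states a rule, and that rule neither reaches the sample nor covers unprescribed use.

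**Conclusion.** The point holds as a minor one. Patients exposed between recruitment and the baseline stool, or taking probiotics on their own account, remain eligible under the criterion as written.

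For the randomised microbiota comparison the consequence is mainly noise: about 2 to 5% more variance if 2 to 6% are exposed and the shift is 1 SD. The loss becomes material (effective n about 30 of 50) only at the far end of the range, 20% exposed with a 2 SD shift, which is beyond the exposure computed for the gap. All of these sizes rest on an assumed interval, assumed rates and an assumed shift.

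Randomisation gives less protection elsewhere. Baseline profiles and within-person change take up the disturbance directly. The symptom–microbiota correlations can be distorted if recent use affects both. That contamination has occurred, or that it biases the treatment comparison, is not established.

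**What to change.** **Patients still to enter.** Reword the exclusion to any use of antibiotics or probiotics, prescribed or not, within the month before the baseline stool sample. Re-check it at the baseline visit before randomisation, and postpone that visit if the criterion is not met. The one-month length is the plan's own; only the anchor and the type of exposure change.

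**Patients already enrolled.** Where use was recorded, run a microbiota sensitivity analysis that leaves out baseline samples taken within one month of use, covering within-person change and the symptom correlations as well as the group comparison.

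**Cost.** One amended sentence, one question at an existing visit, a few baseline visits delayed by up to a month, and one extra analysis. The article expects the study to conclude in May 2025, so the rewording helps only if patients remain to be entered. Otherwise the sensitivity analysis is the part that can still be done.

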#### 2.1.2. Baseline Visit and Randomization of Participants

During the baseline visit, a trained nurse administers a questionnaire to record demographic data and a complete medical history, including alcohol consumption and smoking habits (Supplementary Figure S1). Additionally, participants complete various validated questionnaires specific to each symptom of histamine intolerance (described below). Comprehensive information on dietary habits is collected through a validated 151-item semi-quantitative food frequency questionnaire (FFQ), a seven-day dietary recall (for the seven days prior to the visit), and either a 14-item Mediterranean diet adherence screener (for control diet) or a low-histamine diet screener, administered by trained dieticians in face-to-face interviews [32].

The same trained personnel then collect anthropometric measurements, determine blood pressure (BP), and extract a blood sample to analyze biochemical parameters. Height is measured to the nearest 0.1 cm using a wall-mounted stadiometer, with subjects standing, wearing socks, and maintaining their heads in the horizontal plane. Body weight is recorded to the nearest 0.1 kg, with participants in light clothing, without shoes or accessories, and using a high-quality calibrated scale. Body mass index is calculated by dividing weight (kg) by the square of height (m^2^). Waist circumference is measured midway between the lowest rib and the iliac crest using an anthropometric tape, and hip circumference is measured at the maximum point below the waist, without compressing the skin [33]. BP is taken in triplicate after at least five minutes of rest using a validated semiautomatic oscillometer (Omron HEM-705CP, Hoofddorp, The Netherlands). The clinical analyses include a basic biochemical profile (i.e., glycemia, lipid profile, creatinine, urea, hepatic function parameters, and total proteins and albumin) and serum histamine and tryptase levels. All these analyses are performed in the CORE laboratory of Hospital Clinic following in-house routine procedures and meet all required quality criteria, receiving ISO 9001:2015 certification [34] and ISO 15189:2022 accreditation [35] for some tests.

At this point, participants provide urine and stool baseline samples for the study of metabolomic biomarkers of histamine and intestinal microbiota, respectively (described below). Samples are processed after collection and stored in −80 °C freezers.

Participants are randomized into eight groups, considering both diet and supplementation, as shown in Figure 2. Randomization is conducted using sealed envelopes, with participants selecting one envelope for the dietary intervention and another for the type of supplementation. Once an envelope is chosen, it is removed from the pool.

#### 2.1.3. Dietary Intervention

The low-histamine diet primarily involves the exclusion of foods likely to contain histamine (i.e., fish and its derivatives, fermented products, and certain plant-based foods), as well as foods with high amounts of other biogenic amines, such as citrus fruits, banana, nuts, pumpkin, and zucchini. Although these foods do not contain histamine, they may have significant amounts of putrescine and/or cadaverine, which could trigger the onset of histamine intolerance symptoms due to competition with histamine for degradation by the DAO enzyme [36]. Supplementary Figure S2 contains the dietary recommendations for participants, including a list of foods to consume and to avoid for correct adherence to the low-histamine diet. Participants in the control diet groups continue following their usual dietary habits.

Regarding supplementation, both possible origins of the DAO active ingredient (porcine and vegetal) will be assessed. In order to consider the potential influence of the dose of active ingredient, vegetal DAO supplements at two different doses will be tested. The posology for DAO (regardless of origin and dose) and the placebo involves taking one tablet 20 min before each main meal (three times/day). Porcine DAO supplementation consists of a kidney protein extract (4.2 mg), authorized as a novel food by the European Commission since 2017 [37]. Vegetal DAO supplements are formulated with lyophilized green pea (*Pisum sativum*) sprouts, containing either 4.2 mg or 8.4 mg of the active ingredient per tablet. The placebo tablets consist of microcrystalline cellulose, designed to match the form, size, and color of the DAO supplements. All tablets have an enteric coating to ensure their integrity during passage through the gastric environment. DR Healthcare España S.L.U. (Barcelona, Spain) provides both DAO supplements and placebo tablets.

#### 2.1.4. Follow-Up and Final Visits

The evolution of symptoms, urinary profile of histamine metabolites, and intestinal microbiota composition, as well as anthropometric measurements and blood biochemical parameters, including the basic biochemical profile and histamine and tryptase, are assessed after the first and second month (follow-up visits) and the third month (final visit) of the dietary intervention (Figure 2). Serum DAO activity will also be measured during the final visit.

Dietary compliance is assessed using seven-day food records and adherence tests for the low-histamine diet or Mediterranean diet [32]. Unlike the validated Mediterranean diet adherence screener, there is no standard test for assessing compliance with a low-histamine diet. The present research will validate the low-histamine diet adherence test prepared *ad hoc* for this study.

Throughout the intervention period, participants receive a phone call every two weeks to assess correct adherence to the study protocol and to monitor for any unexpected secondary effects.

### 2.2. Study Outcomes

#### 2.2.1. Symptoms of Histamine Intolerance

Symptoms related to histamine intolerance, listed in Figure 1, are evaluated through specific validated questionnaires as follows: (a) gastrointestinal manifestations are assessed by the Gastrointestinal Quality of Life Index (GIQLI) and Bristol Stool Scale [38,39]; (b) headaches by the Migraine Disability Assessment Scale (MIDAS) and Headache Impact Test (HIT-6) [40,41]; (c) respiratory symptoms by the Rhinoconjunctivitis Quality of Life Questionnaire (RQLQ) and Nasosinusual Symptoms Questionnaire (SNOT-22); and (d) dermatological manifestations by SCORing Atopic Dermatitis (SCORAD), the Itch Severity Scale (ISS), Quality of Life Index for Atopic Dermatitis (QoLIAD), and Dermatology Life Quality Index (DLQI) [42,43,44,45,46]. Additionally, the general quality of life of patients is assessed using the SF-36 Health Questionnaire [47].

Data obtained from these questionnaires will be used to evaluate the effectiveness of the dietary treatment in the improvement or remission of patient symptomatology. Differences among the study groups will be determined using covariance analysis with baseline parameters as covariates. A multivariate analysis adjusted for age, sex, and clinical parameters with significant baseline differences among groups will also be applied. These differences will be expressed as means (95% confidence intervals).

All collected data regarding symptomatology will also be used to assess potential correlations with other study outcomes, such the composition of intestinal microbiota, the urinary profile of histamine metabolites, serum DAO activity, plasma histamine levels, and DAO-encoding gene variants.

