## 2. Materials and Methods

### 2.1. Study Design

This prospective, unicentric, double-blind, randomized, and placebo-controlled trial is being performed by a multidisciplinary team of researchers from the Food Bioactive Amines and Polyamines research group at the Food and Nutrition Campus, University of Barcelona, and the Cardiovascular Risk, Nutrition, and Aging research group at the August Pi i Sunyer Biomedical Research Institute (IDIBAPS) of the Hospital Clínic de Barcelona. The study commenced in June 2022 and is expected to conclude in May 2025.

The study design is outlined in Figure 2. In this protocol, participants are randomized into eight study groups (50 individuals/group), based on combinations of diet (low-histamine or control diet) and supplementation (placebo, porcine DAO, and two different doses of plant-based DAO). The intervention period lasts three months.

The sample size is calculated considering the average number of symptoms reported by histamine-intolerant patients and the standard deviation (11.1 symptoms/patient ± 4.8) [6]. To detect a variation in at least two symptoms per patient, assuming an alpha risk of 0.05 and a beta risk of 0.02 in a bilateral contrast, a minimum of 42 participants per group is required. To accommodate a 10% drop-out rate, 50 participants will be recruited for each group. Therefore, as the study includes eight intervention groups, the total number of participants is 400.

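### The sample size rests on a count of symptoms, but the outcome section names no such count and ranks none of its eleven questionnaires as primary

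*Protocol article*

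**What the plan says.** **Sizing (section 2.1).** "The sample size is calculated considering the average number of symptoms reported by histamine-intolerant patients and the standard deviation". The mean is 11.1 and the SD 4.8. The target is given as "To detect a variation in at least two symptoms per patient". The error rates behind the calculation are two-sided alpha 0.05 and, as printed, beta 0.02. From this, "a minimum of 42 participants per group is required". The allowance for losses is then stated separately: "To accommodate a 10% drop-out rate, 50 participants will be recruited for each group". That makes 400 over eight groups.

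**Objective (Introduction).** The main objective is symptom improvement over three months. No measure, time point or contrast is attached to it.

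**Outcomes (section 2.2.1).** Symptoms are measured with GIQLI, Bristol, MIDAS, HIT-6, RQLQ, SNOT-22, SCORAD, ISS, QoLIAD and DLQI. SF-36 is added for general quality of life. Then: "Data obtained from these questionnaires will be used to evaluate the effectiveness of the dietary treatment in the improvement or remission of patient symptomatology". The method is covariance analysis among the groups with baseline covariates, plus a further adjusted analysis, reported as means with 95% intervals.

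**Schedule.** Section 2.1.4 has the evolution of symptoms assessed at months 1, 2 and 3 without defining the measure. The only general symptom questionnaire in the text (Supplementary Figure S1) is cited for eligibility in section 2.1.1 and for the baseline history in section 2.1.2.

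**The concern.** A sample size is a statement about one variable, one contrast and one time point. Here the variable that was sized does not appear among the outcomes, and the variables that will decide efficacy were not sized. Two consequences follow.

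- The power statement cannot be carried over to any of the questionnaires, because a difference of two symptoms against an SD of 4.8 has no counterpart on their scales.
- With eleven unranked instruments and three post-baseline visits, nothing in the article fixes in advance which result answers the main objective. A favourable result on any one of them could be presented as the answer.

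**Working it through.** **1. The plan's own figure.** Inputs from section 2.1: difference 2, SD 4.8, two-sided alpha 0.05, beta 0.02.

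Two-group formula: n per group = 2 × (SD/difference)² × (z₁₋α/₂ + z₁₋β)².

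- Beta 0.02: 2 × 5.76 × (1.960 + 2.054)² = 185.6, so 186.
- Beta 0.20, in case 0.02 is a misprint: 2 × 5.76 × (1.960 + 0.842)² = 90.4, so 91.
- One-sample or paired formula with SD 4.8 (half of the above): 93 at beta 0.02 and 46 at beta 0.20.

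None of these gives 42. That is a separate defect, but it bears on what power can be claimed once a primary outcome is named. The drop-out step is sound: 42/0.9 = 46.7, so 47, and 50 covers it.

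**2. Power for the quantity that was sized.** Power ≈ Φ(difference / (SD × √(2/n)) − 1.96).

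| Comparison | n per side | Power for 2 symptoms |
|---|---|---|
| Two single groups | 42 | 48% |
| Two single groups (50 less 10%) | 45 | 51% |
| Two single groups | 50 | 55% |
| One active supplement vs placebo, pooled over both diets (2 × 42) | 84 | 77% |
| Low-histamine vs control diet, pooled over supplements (4 × 42) | 168 | 97% |

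At 45 per group: 2 / (4.8 × √(2/45)) = 1.976, and Φ(1.976 − 1.960) = 0.507. The pooled rows assume that the two-symptom difference holds as an average over the pooled groups. No row credits baseline adjustment, because the article gives no baseline-to-follow-up correlation.

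**3. Sized quantity against analysed quantities.**

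| | Section 2.1 | Section 2.2.1 |
|---|---|---|
| Variable | number of symptoms per patient | 10 domain instruments + SF-36 = 11 |
| SD | 4.8 | none given |
| Target difference | 2 | none given |
| Primary designation | none | none |

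Power cannot be computed for any of the eleven from what the article gives.

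**4. Error rate with no primary.** Assumption: each instrument is tested at 0.05, unadjusted, at one visit.

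- Independent scales: 1 − 0.95¹¹ = 0.431.
- Equal correlation between scales, one two-sided contrast per scale (simulation): about 37% at 0.3, 30% at 0.5, 22% at 0.7 and 13% at 0.9.
- Eight-group 7-df test per scale, 45 per group (simulation): about 43%, 33% and 25% at correlations 0, 0.5 and 0.7.

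The correlations are assumed; the article gives none. For scale, a Bonferroni level over eleven is 0.05/11 = 0.0045.

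**The case against.** The best defence is that this is a condensed article with an analysis plan not shown. Multiplicity rules and the ordering of contrasts commonly sit there. Alpha 0.05 appears only in the sample-size paragraph, and section 2.2.1 promises estimates with intervals, not a decision rule. This stands as far as it goes: the 22–43% figures are conditional, and the absence of an adjustment rule is not in itself the finding. It does not reach the mismatch, because the article prints both the sizing variable and the efficacy variables, and they differ.

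A count may also be collected: monthly assessment of symptoms is planned, and Figure 2 and Supplementary Figure S1 are not shown. So the fair statement is that the text does not identify a count as an outcome, not that none exists. Equal standing of the instruments is likewise inferred from the lack of ranking, and SF-36 is introduced as an addition.

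A reader might infer two stronger points that the article does not support.

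- *Hundreds of pairwise tests.* All 28 pairs of eight groups on eleven scales would be 308 tests, with about 15 expected below 0.05 by chance (308 × 0.05 = 15.4). No section plans this. The Abstract and Discussion speak of separate diet and supplement effects and their synergy, which reads as factorial.
- *Dilution by unaffected participants.* Eligibility asks for "symptoms associated with histamine intolerance in two or more organs or systems", so some participants could have no complaint in a domain that is scored. But two is a minimum, a mean of 11.1 symptoms is compatible with wider involvement, and no domain-level prevalence is given. An effect averaged over everyone randomised is a legitimate target. At most this supports a sensitivity analysis.

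**Conclusion.** The concern holds as an internal mismatch. The trial is sized on a symptom count that the outcome section does not name, and efficacy is to be judged on eleven unranked questionnaires for which nothing was sized. The stated power therefore attaches to no named efficacy outcome, and the main objective has no single designated test. That conclusion needs no assumption beyond the text of sections 2.1 and 2.2.1.

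The false-positive figures (about 43% under independence, roughly 22–33% at correlation 0.5–0.7, one visit) rest on unadjusted testing at 0.05 and on assumed correlations. They show what is at risk if no rule exists, not what the trial has committed to. Even if the count is adopted as primary, the stated SD supports only about 51% power for two symptoms between two groups of 45.

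**What to change.** Before unblinding, amend the protocol to name one primary outcome, one time point and the primary contrast or contrasts.

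- **If the symptom questionnaire in Supplementary Figure S1 is repeated at follow-up:** make the number of symptoms at month 3, adjusted for baseline, the single primary outcome. Pre-specify the contrast, for example the factorial diet main effect and supplement versus placebo pooled over diets, and say how alpha is shared if there is more than one. The Discussion already allows combined-group analyses as secondary; this would make the pooled contrast primary. The eleven questionnaires become secondary, with an adjustment such as Holm across instruments for each contrast.
- **If counts were not repeated:** name one instrument that was collected as primary, and state its SD, target difference and power. The trial began in June 2022, so missing month-3 counts cannot be recovered for participants who have finished.
- **In either case:** replace the current power statement with one that follows from its inputs for the chosen outcome and contrast. Any analysis restricted to participants with a given system affected at baseline should be labelled a sensitivity analysis.

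The cost is wording and a recalculation, with no new procedure where counts already exist. The secondary scales face a stricter threshold, and the stated power will look less favourable than it does now.

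### In the additional adjusted symptom analysis, clinical covariates beyond age and sex are chosen by baseline significance tests, which select by chance rather than by prognostic value

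*Protocol article*

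**What the plan says.** Section 2.2.1 gives two adjusted analyses of the symptom questionnaires. The first reads: "Differences among the study groups will be determined using covariance analysis with baseline parameters as covariates". It does not name the covariates. The second follows directly: "A multivariate analysis adjusted for age, sex, and clinical parameters with significant baseline differences among groups will also be applied". Neither is labelled primary. No list of candidate clinical parameters and no threshold for a significant baseline difference is given.

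Section 2.1.2 describes the allocation: "Randomization is conducted using sealed envelopes, with participants selecting one envelope for the dietary intervention and another for the type of supplementation". The same section shows how many parameters could be candidates. They include anthropometry, blood pressure, serum histamine and tryptase, and the routine laboratory panel: "The clinical analyses include a basic biochemical profile (i.e., glycemia, lipid profile, creatinine, urea, hepatic function parameters, and total proteins and albumin").

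**The concern.** A baseline significance test in a randomised trial asks whether chance produced the difference. If randomisation was carried out properly, the answer is already known to be yes. The test says nothing about whether the variable predicts symptoms, and prediction is the reason to adjust for it. Used as an entry rule, it gives a liver enzyme and a strong predictor of symptoms the same chance of entering the model.

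Two things are at stake. First, precision available from variables already measured is mostly not used, in a trial whose Discussion names small group size as its main limitation. Second, the form of the second model depends on the trial's own data, so it cannot be known in advance. The rule is written into the protocol, so this is not a detail left to an analysis plan; a plan that follows the protocol would inherit it.

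**Working it through.** The plan gives no figure for this rule, so there is none to reproduce. The sample-size inputs are used below only to set a scale.

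**Inputs**
- Eight groups of 50 with 10% drop-out (section 2.1): 50 × 0.90 = 45 per group.
- Difference of 2 symptoms, SD 4.8 (section 2.1): 2/4.8 = 0.417 SD.
- Significance level for the baseline tests: not stated. Assumed 0.05, the level in the sample-size statement ("assuming an alpha risk of 0.05 and a beta risk of 0.02 in a bilateral contrast").
- Number of candidates K and correlation ρ of a covariate with the outcome: not in the document; ranges assumed.

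**Step 1: chance that a given covariate enters.** Under random allocation this is 0.05 whatever ρ is, so exclusion has probability 1 − 0.05 = 0.95. A simulation (6,000 runs for each ρ, eight groups of 45, one covariate entered only if its baseline ANOVA gave p < 0.05) found entry rates of 0.050, 0.053 and 0.047 at ρ = 0.3, 0.5 and 0.7.

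**Step 2: chance that at least one of K enters by luck.** For independent tests this is 1 − 0.95^K:
- K = 5: 23%
- K = 10: 40%
- K = 20: 64%
- K = 30: 79%

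Lipid fractions, liver tests, and weight with waist are correlated, so the true figures are somewhat lower.

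**Step 3: precision.** The same simulation, for one pairwise contrast at a difference of 0.417 SD, gave this power:

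| ρ (assumed) | No adjustment | Protocol's rule | Covariate fixed in advance |
|---|---|---|---|
| 0.3 | 50% | 51% | 54% |
| 0.5 | 50% | 51% | 62% |
| 0.7 | 50% | 51% | 79% |

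A normal approximation agrees. The standardised difference is 0.417/√(2/45) = 1.976, so unadjusted power is Φ(1.976 − 1.96) = 51%. With a covariate at ρ = 0.5 it is Φ(1.976/√0.75 − 1.96) = Φ(0.322) = 63%.

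**Step 4: precision if the baseline score is already in the model.** The table compares with no adjustment at all. Suppose instead that the baseline score is adjusted for and correlates 0.5 with the outcome, and that the further covariate correlates r with both. Its squared partial correlation is (0.5r)²/[0.75(1 − r²)]:
- r = 0.3: 0.0225/0.6825 = 3%. Power is Φ(1.976/√(0.75 × 0.967) − 1.96) = 64%.
- r = 0.5: 0.0625/0.5625 = 11%. Power is Φ(1.976/√(0.75 × 0.889) − 1.96) = 68%.

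Both compare with 63% from the baseline score alone, a gain of roughly 1 to 5 percentage points.

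**Step 5: type I error.** With no true difference, the rule rejected in 0.052, 0.048 and 0.047 of runs at the three values of ρ, against a nominal 0.05.

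**The case against.** The strongest reply is that the rule has a narrow reach. It governs an additional analysis. The covariance analysis in the preceding sentence stands apart from it and, on the ordinary reading, already carries the baseline value of each questionnaire. Age and sex are in the second model in any case. A covariate that enters by chance does not bias a randomised comparison. All of this stands, and it limits the point to one sentence of the plan. It does not rescue that sentence, because the entry criterion is unrelated to the purpose of adjustment.

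A reader might go further in four ways that the document does not support:
- **Inflated error rate.** A data-dependent model invites this inference, but step 5 shows average type I error near 5%.
- **A large loss of precision.** Correlations of 0.3 to 0.5 would imply 9% to 25% less residual variance (0.3² to 0.5²). Those correlations are assumed, and the figure ignores baseline adjustment; step 4 gives about 3% to 11% under its own assumptions.
- **Baseline symptom burden being dropped.** This cannot be claimed for the first analysis, whose covariates are unnamed but plausibly include it.
- **Recruiting unit being wrongly omitted.** Section 2.1.1 says "Participants are recruited during medical visits in the Allergology, Digestive, Internal Medicine, or Dermatology units". It does not say that unit predicts response or is recorded as a data item, and unit is not clearly a clinical parameter within the rule.

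**Conclusion.** The point holds for the additional multivariate analysis only. Its clinical covariates beyond age and sex are selected by a criterion that, under random allocation, is chance. Each candidate is left out about 95% of the time whatever its prognostic value, and at least one enters by luck with probability of about 40% to 64% for 10 to 20 candidates. That range assumes the number of candidates, independence and a 0.05 threshold; correlation among the candidates lowers it somewhat.

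The cost is a model not fixed in advance and forgone precision. For a single covariate the loss in power ranges from a point or two to substantial, depending on assumed correlations and on whether the baseline score is already in the model. The first covariance analysis is not undermined, and inflation of average type I error is not shown. The simulation covers one candidate covariate under a mechanical rule.

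**What to change.** Replace the selection rule with a covariate list fixed before unblinding and chosen on prognostic grounds from data already collected: the baseline value of each outcome, age, sex and, for example, DAO status at screening. Recruiting unit can be added if it is recorded. State that baseline significance tests will not be used to select covariates, and report baseline imbalance descriptively.

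The cost is about one sentence in the protocol or analysis plan. Baseline questionnaires and demographic data are collected at the baseline visit (section 2.1.2), and DAO activity and genotype at screening (section 2.1.1), so no new data or participants are needed. Only recruiting unit would need a check that it is held as a data item.
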